### 7.9.5 Stratification and randomization

We will stratify our randomization by timing of ART initiation (during current pregnancy / pre-pregnancy). Participants will be assigned with equal probability to one of the two treatment groups. A statistician not otherwise associated with the study will design the randomization scheme using random permuted blocks and taking into account the stratification scheme.

### 7.9.6 Analysis plan

Our **primary outcome** will be the composite outcome comprising delivery prior to 37 weeks completed gestation or stillbirth at any gestational age. At the time of enrollment, each participant will be assigned an estimated delivery date (EDD) by ultrasound biometry.

Randomized women who deliver (1) a live infant prior to 37 weeks of gestation or (2) a stillborn infant at any gestational age will be categorized as having met the primary outcome.

The primary analysis will employ the intent-to-treat principle, wherein each mother-infant pair will be analyzed according to randomization assignment regardless of whether the mother actually complied with study procedures. The primary comparison between the two trial arms will be based on the estimated risk ratio of the primary outcome. The estimated risk of the primary outcome will be computed in each arm using the Kaplan-Meier method to adjust for loss-to-follow-up, where mother-infant pairs who drop out of the trial prior to the primary outcome or live-birth of full-term infant will be right censored at their last study visit. A Z-statistic will be constructed by taking the difference in the estimated log risks divided by the corresponding estimated standard error (using the Greenwood estimator). As a sensitivity analysis, a Cox proportional hazards model, stratified by timing of ART initiation (during current pregnancy / pre-pregnancy) will be fit to estimate the hazard ratio between randomization arms; the estimated hazard ratio is anticipated to be similar to the estimated risk ratio given that the primary outcome is relatively rare (<20%). In a secondary analysis, we will compare the risk of spontaneous preterm birth across randomized groups, treating provider-initiated preterm births as a competing risk and estimating the risk of the outcomes in each randomized group using the Aalen-Johannson method. To explore comparability with other published studies, we will evaluate the effect of excluding events that occur prior to 20 weeks in a sensitivity analysis.

Subgroup analyses will assess whether the effect of 17P differed within levels of the randomization stratification factor. For timing of ART initiation, effect modification will be assessed by fitting Cox proportional hazards models that include as covariates randomization arm, the stratification factor, and a product term. A likelihood ratio test of the product term coefficient will be used to assess possible effect modification. To adjust for multiple comparisons, the likelihood ratio tests will be considered significant if  $p < 0.05/2$ . If the effect modification tests are significant, hazard ratios will be estimated separately within levels of the factor (e.g., hazard ratios of 17P versus placebo for (i) mothers on pre-pregnancy ART and (ii) mothers not on pre-pregnancy ART).

To assess the efficacy of 17P, a per-protocol analysis of the primary outcome will also be conducted that censors participants who fail to comply with their randomization assignment (defined here as missing two injections of study product in a row), and then reweights the data to account for possible informative censoring by noncompliance using inverse-probability (IP) weights. We have previously used this and related methods to construct a consistent estimator of the per-protocol effect under the assumption that we have measured and correctly-adjusted for the common causes of noncompliance and the outcome. The set of measured possible common causes includes demographic, medical, and obstetrical factors. We will construct IP weights using pooled logistic regression (pooling over time), with continuous variables fit using flexible restricted splines. We will explore the sensitivity to IP weight estimation.

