### 7.5 Study procedures

#### 7.5.1 Screening

Our recruitment activities will begin with community sensitization in the catchment area of the recruitment clinics to educate community members about the trial and encourage early presentation for ultrasound. This community and clinic sensitization may be underway prior to initiation of this project as a result of other programs in the catchment areas.

Trained study staff will conduct health talks at the study site, focusing on the importance of antenatal care and possible prevention of preterm or early delivery, with emphasis on study inclusion and exclusion criteria. Staff will provide interested women with additional information and referrals to the study clinic for eligibility assessment.

Potential participants will be identified at their first antenatal visit. Women may be enrolled any time prior to 24 /7 gestational weeks. Following a prescreening consent process, a dating ultrasound will be conducted per standard of care to confirm pregnancy location, viability, number of fetuses, and, among women within the recruitment window, cervical length

according to the method described by Iams et al. Those who meet preliminary eligibility criteria who are interested in participating will complete the study informed consent process in English, Nyanja, or Bemba, depending on their language preference. Trial participation will be offered to all HIV-infected pregnant women who are determined to meet the listed inclusion and exclusion criteria.

After consenting for participation, women will be administered a series of questionnaires that gather targeted information on relevant demographics, health and risk behaviors, medical and obstetrical history, medication use, stress, and nutrition. If not already done so in routine antenatal care, participants will undergo a physical exam, including testing for urinary tract infections and proteinuria, anemia, syphilis, and HIV (as outlined in TABLE 1), all of which are recommended as part of routine antenatal care. Treatment of HIV and any obstetric complications will also be according to standard practice in Zambia.

Blood, urine, and vaginal swabs will be collected as detailed in Table 1.

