### 7.9.4 Trial sample size

In summary, we postulate that 17P will reduce the proportion of HIV-infected women experiencing the composite endpoint by 38% (from 24% to 15%). We used SAS 9.3 (SAS, Cary, NC) to determine that a trial with 325 patients per arm would have 80% power to detect this effect size (based on a 2-sided Fisher's exact test at the 0.05 significance level; FIGURE 2). To **allow for up to 15% follow-up loss** (although prior experience from our sites suggests it will be half this) and to account for uncertainty in our estimates of baseline event probability (p1) and relative efficacy of the intervention, we plan to enroll **400 women per arm** in the trial. As FIGURE 2 indicates, the study will have 80% power to demonstrate any combination of baseline event rate and relative efficacy that falls below the red horizontal line (after accounting for follow-up losses and any missing outcomes).

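### The primary risk-ratio test ignores the ART-timing strata used in randomisation, so its standard error is somewhat too large if ART timing is prognostic

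*Protocol*

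**What the plan says.** Section 7.9.5 of the protocol: "We will stratify our randomization by timing of ART initiation (during current pregnancy / pre-pregnancy"), using permuted blocks and 1:1 allocation.

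Section 7.9.6 fixes the primary comparison in detail. The risk of the composite outcome is estimated once per arm by Kaplan-Meier, with women who drop out censored at their last visit. Then "A Z-statistic will be constructed by taking the difference in the estimated log risks divided by the corresponding estimated standard error", with Greenwood's variance. No stratum or baseline covariate enters.

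The same section uses ART timing in two other places: as the stratifying variable of a sensitivity Cox model, and as the factor in the subgroup interaction test.

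Sections 1.0 and 5.2 ask, as a trial question and a secondary objective, whether women who start ART in pregnancy have a higher risk than women already on ART at conception.

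On size, section 7.9.4 states that "a trial with 325 patients per arm would have 80% power to detect this effect size". The test assumed there is Fisher's exact test, two-sided at 5%. The plan enrols 400 per arm to "allow for up to 15% follow-up loss" and for uncertainty in its inputs.

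**The concern.** Stratified randomisation balances the arms on ART timing, which removes chance imbalance on that factor from the true sampling variance of the treatment effect. A standard error computed from one pooled risk per arm still counts that imbalance. If the outcome risk differs between the strata, the reported interval is wider than the design warrants and the nominal 5% test rejects less often than 5% under the null.

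The protocol itself names the primary estimator, test statistic and variance, so this is not a detail left open for the SAP. Nor does the stratified Cox model fill the gap. It estimates a hazard ratio, which under the design rates (24% v 14.9%) and proportional hazards would be ln(1 − 0.1488)/ln(1 − 0.24) = 0.587 against a risk ratio of 0.62. No planned overall analysis of the primary measure respects the strata.

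What is at stake is precision, and some protection against dropout patterns that differ between arms. The validity of the test is not in question.

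**Working it through.** **1. The plan's own figure.** Inputs from section 7.9.4: 24% v 15%, two-sided alpha 0.05, power 80%. The two-proportion formula gives 304 per arm, and with continuity correction 325, as stated. Exact enumeration of Fisher's test at 325 per arm gives power 80.3%. With 15% loss, 325/0.85 = 382.4, so 383 are needed and 400 covers it; 400 × 0.85 = 340 evaluable. The sample size is sound.

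**2. Variance of the log risk ratio.** Per arm it is (1 − p)/(np). With p = 0.24 and 0.24 × 0.62 = 0.1488:
- placebo: 0.76/0.24 = 3.167
- 17P: 0.8512/0.1488 = 5.720
- sum: 8.887, so at n = 340 the pooled SE is √(8.887/340) = 0.1617.

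**3. Part lying between strata.** The protocol gives no stratum shares or risks. Assumed here: equal strata and a constant risk ratio of 0.62. In each arm the between-stratum part of (1 − p)/p is (d/p)², where d is half the gap between the stratum risks. With a constant risk ratio, d/p is the same in both arms.

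| Control risks (assumed) | (d/p)² per arm | Share of Var(log RR) removed | Equivalent women per arm, 340/(1 − share) − 340 |
|---|---|---|---|
| 30% v 18% | (0.06/0.24)² = 0.0625 | 0.125/8.887 = 1.4% | about 5 |
| 36% v 12% (extreme) | (0.12/0.24)² = 0.25 | 0.50/8.887 = 5.6% | about 20 |

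**4. Power at 340 per arm.** With |ln 0.62| = 0.478:
- pooled SE: 0.478/0.1617 − 1.96 = 0.997, power 84.1%
- stratified, 30% v 18%: SE 0.1617 × √0.986 = 0.1605, power 84.6%
- stratified, 36% v 12%: SE 0.1617 × √0.944 = 0.1571, power 86.1%.

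The 84.1% takes the pooled SE as the true spread. Stratified randomisation already makes the true spread smaller, so the pooled test's real power is Φ(0.997/√0.986) = 84.2% or Φ(0.997/√0.944) = 84.8%. The gain from changing only the analysis is therefore about 0.3 to 1.3 points.

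**5. True alpha of the pooled test.** Under the null both arms have the control risks. The between-stratum share of p(1 − p) = 0.1824 is then 0.0036/0.1824 = 2.0% or 0.0144/0.1824 = 7.9%. The effective critical values are 1.96/√0.980 = 1.980 and 1.96/√0.921 = 2.042, giving alpha of about 0.048 and 0.041.

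**6. Wider range of assumptions.** With 24% v 15%, a risk ratio between ART strata of 1.2 to 2.2 and a smaller-to-equal stratum share of 20% to 50%, the share removed is 0.1% to 3.7%, or about 0.5 to 13 women per arm. Power goes from 83.0% to between 83.1% and 84.4%. The 2.2 is borrowed from section 3.0, where it refers to receipt of ART, not its timing.

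**7. Dropout.** Taking 30% v 18%, equal strata, a true ratio of 0.62 and dropout at entry:
- same pattern in both arms: the placebo and 17P risks shift by the same factor, so the ratio stays at 0.62
- 20%/10% (high-/low-risk stratum) on placebo, 10%/10% on 17P: placebo risk (0.8 × 0.30 + 0.9 × 0.18)/1.7 = 0.2365, ratio 0.1488/0.2365 = 0.629
- 30%/5% on placebo, 10%/10% on 17P: (0.7 × 0.30 + 0.95 × 0.18)/1.65 = 0.2309, ratio 0.644.

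**The case against.** The strongest reply is that nothing here is an error. An unadjusted intention-to-treat risk ratio after stratified randomisation is valid, errs on the conservative side, and the stratum is not ignored altogether. That stands, and it makes this a point about efficiency. It does not remove the point, because the plan gives up precision that its own randomisation has already paid for.

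A reader might infer more, and the protocol does not support it:

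- **That power is already marginal.** It is about 83-84% at the full 15% loss, and section 7.9.4 expects about half that loss.
- **That the rarity premise for the Cox model (below 20%) contradicts the 24% baseline rate.** The 24% is the placebo rate. The average over both arms is (24% + 14.9%)/2 = 19.4%, and the text only anticipates that the two measures will be similar.
- **That the pooled ratio is biased whenever dropout and risk both differ by ART timing.** With the same dropout pattern in both arms and a constant risk ratio it is not. A shift needs the pattern to differ by arm as well, which masking makes less likely. Stratum-specific estimates in turn still assume non-informative dropout within strata.
- **That the protocol expects ART timing to be prognostic.** It asks whether it is.
- **That the gain is larger.** Applying the control-arm shares of 2.0% and 7.9% to both arms would give about 7 and 29 women per arm, but the share in the 17P arm is lower (1.1% and 4.4%) and that arm contributes more of the variance.
- **That leaving out cervical length is a fault of the same kind.** Screening measures, "among women within the recruitment window, cervical length", so values may be missing for women screened early. Its prognostic strength is not given, and covariate-adjusted supporting analyses are ordinary SAP content.

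**Conclusion.** The point holds as a modest loss of efficiency. The primary test does not match the stratified randomisation, and if ART timing is prognostic its standard error is somewhat too large. With equal strata, a constant risk ratio of 0.62 and control risks from 30% v 18% to 36% v 12%, the excess is about 1.4% to 5.6% of the variance. The upper end needs a threefold risk ratio between strata, for which the protocol offers no support. If ART timing turns out not to be prognostic, nothing is lost by the pooled test and almost nothing by stratifying. Type I error is not inflated and the sample size calculation is unaffected. The change is worth making because it is nearly free and keeps the same marginal risk ratio as the target.

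**What to change.** In section 7.9.6, define the primary analysis as follows. Estimate the Kaplan-Meier risk by arm within each of the two ART-timing strata. Average the stratum risks in each arm using the stratum shares of the whole trial population. Test the log of the ratio of these standardised risks, with the Greenwood variances combined over strata and carried to the log scale. Keep the pooled comparison as a sensitivity analysis.

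This also protects the ratio when dropout by stratum differs between arms, provided dropout within each stratum is non-informative.

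A supporting risk-ratio analysis adjusted for cervical length is optional. If it is added, state how missing values will be handled.

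The cost is a few sentences in the protocol and SAP and slightly more programming, with no new data. The change should be made before unblinding so that it cannot look data-driven.

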## **5.2 Secondary objectives**

- To assess, through a subgroup analysis, whether 17P will reduce the risk of the composite primary outcome among women either (a) newly initiating ART or (b) continuing ART that was started prior to conception
- To assess the effect of timing of ART initiation on risk of the composite primary outcome and its components by comparing women newly starting ART to those who initiated ART prior to conception (non-randomized comparison), and controlling for possible confounders (e.g., CD4 count, viral load, ART regimen).
- To assess the extent to which exclusion of provider-initiated PTB phenotypes modify (a) the observed efficacy (if any) of 17P to prevent the composite primary outcome and (b) its components and any association between timing of ART initiation and PTB.

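### The interaction test uses 0.05/2 with only one test in the plan, and stratum-specific effects are planned only after a significant result, although the first secondary objective asks for them without condition

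*Protocol*

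**What the plan says.** The relevant statements stand in four places of the Protocol.

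- **Section 5.2, first secondary objective:** "To assess, through a subgroup analysis, whether 17P will reduce the risk of the composite primary outcome among women either (a) newly initiating ART". Its second group is women whose ART predates the pregnancy. No condition is attached.
- **Section 7.9.5:** "We will stratify our randomization by timing of ART initiation (during current pregnancy / pre-pregnancy"). This is the only stratification factor named.
- **Section 7.9.6, test:** "Subgroup analyses will assess whether the effect of 17P differed within levels of the randomization stratification factor". The Cox model contains arm, the factor and their product, and "A likelihood ratio test of the product term coefficient will be used to assess possible effect modification". The threshold is set in the next sentence of that section, which reads: "To adjust for multiple comparisons, the likelihood ratio tests will be considered significant if" p is below 0.05/2.
- **Section 7.9.6, estimation:** "If the effect modification tests are significant, hazard ratios will be estimated separately within levels of the factor".

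Section 7.9.4 holds the Protocol's only power figure, 325 women per arm for the overall comparison. No power is given for the interaction test or for the strata.

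**The concern.** There are two separate difficulties.

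The first is the divisor. Two arms and one two-level factor give one product term and one test. A Bonferroni divisor of 2 needs a second test in the same family, and the Protocol names none. The plural in the sentence that sets the threshold does not match the single factor in the sentences around it.

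The second, and the more consequential, is the condition on estimation. The objective is about the effect of 17P within each ART-timing group. The test asks a different question: whether the two effects differ. If 17P worked equally well in both groups, the answer to the objective would be yes twice, yet that is the situation in which the plan would almost never call for the two estimates.

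At stake is whether a prespecified secondary objective, tied to the stratification factor, gets the estimates it asks for. There is also a selection effect: stratum estimates shown only after a significant interaction come from the trials in which the observed difference happened to be large, so they overstate it on average.

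**Working it through.** **Step 1. Count the tests.** Section 7.9.5: one factor, two levels. Section 7.9.6: one product term. Degrees of freedom: (2 − 1) × (2 − 1) = 1. A Bonferroni level for one test is 0.05/1 = 0.05, against the 0.025 written.

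**Step 2. Reproduce the Protocol's own figure.** Section 7.9.4 postulates a reduction "by 38% (from 24% to 15"%) with 80% power, two-sided Fisher's exact test at 0.05. The pooled formula gives 303.0 per arm (304 rounded up). The continuity correction multiplies this by ¼[1 + √(1 + 4/(303.0 × 0.09))]² = 1.072, giving 324.9, so 325. Exact Fisher power at 325 is 80.3%. The design figure is confirmed. Enrolment of 400 less 15% loss leaves 400 × 0.85 = 340 evaluable per arm.

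**Step 3. Chance that the interaction test is significant.**

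From the Protocol: control risk 24%, risk ratio (RR) 0.62, 340 per arm after full loss.

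Assumed, because the Protocol does not give them: the same 24% control risk in both strata, full effect in one stratum and none in the other (RR 0.62 against 1.0), and the stratum split.

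On the hazard scale, which matches the planned Cox model, I use a Wald approximation to the likelihood ratio test:

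- variance of the difference in log hazard ratios ≈ sum of 1/events over the four arm-by-stratum cells
- hazard ratio in a stratum = ln(1 − p₁)/ln(1 − p₀)
- power ≈ Φ(|difference|/SE − z), with z = 2.241 at 0.025 and 1.960 at 0.05

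50:50 split, so 170 women per cell:

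- Events: 170 × 0.24 = 40.8 in three cells, and 170 × 0.1488 = 25.3 in the fourth.
- SE = √(3/40.8 + 1/25.3) = 0.336.
- Difference = |ln(ln 0.8512 / ln 0.76)| = |ln 0.587| = 0.533.
- Power at 0.025: Φ(0.533/0.336 − 2.241) = 25.6%.
- Power at 0.05: 35.4%.

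Check on the risk-ratio scale, with variance (1 − p)/(np) per cell: SE = √(3 × 0.01863 + 0.03365) = 0.299, |ln 0.62| = 0.478, power 26.0% and 35.9%. The two scales agree closely.

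Other splits, 340 per arm, hazard scale:

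| Split | Stratum with the effect | at 0.025 | at 0.05 |
|---|---|---|---|
| 50:50 | either | 25.6% | 35.4% |
| 30:70 | smaller | 20.4% | 29.3% |
| 30:70 | larger | 22.7% | 32.0% |
| 20:80 | smaller | 15.4% | 23.0% |
| 20:80 | larger | 17.9% | 26.2% |

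**Step 4. Vary the assumptions (hazard scale).**

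- No loss, 400 evaluable per arm, 50:50: 30.0% at 0.025 and 40.5% at 0.05.
- Same effect in both strata: 2.5% and 5%, by definition of the level.
- RR 0.50 against 1.0, 340 per arm, at 0.025: 28% (20:80, effect in the smaller stratum) to 48% (50:50). With 400 per arm and 50:50: 55%.
- RR 0.40 against 1.0, 340 per arm, at 0.025: 41% to 69% over the same splits.

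**Step 5. Selection effect.** At 50:50 on the risk-ratio scale, significance at 0.025 needs an observed ratio of risk ratios below exp(−2.241 × 0.299) = 0.51 (or above its reciprocal), when the true ratio is 0.62. Every estimate in the expected direction that passes is therefore more extreme than the truth. With unequal strata the threshold is further out: at 30:70 with the effect in the smaller stratum (SE 0.337) it is 0.47.

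**The case against.** The best case for the current text has four parts.

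*Testing before presenting is a recognised safeguard.* It discourages over-reading of subgroups. That is a good reason to make a claim of effect modification depend on the test. It is a weaker reason to make the estimates themselves depend on it when the objective asks for them.

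*Nothing is forbidden.* A reader might infer that the subgroup results would be withheld, or that they could be reported only after a significant test. The Protocol does not say so. It plans separate estimates in one case and is silent on the other. The fair description is that the estimates are not planned otherwise.

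*The estimates exist anyway.* A reader might also infer that no subgroup estimate would be produced and the objective would go unanswered. That is too strong. The Cox model with the product term is fitted unconditionally. With ART timing coded 0/1, its arm coefficient is the log hazard ratio in one stratum, and arm plus product gives the other. The overall result and the Cox analysis stratified by ART timing also bear on both groups. What is missing is a commitment to present the two stratum effects with their confidence intervals.

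*The stricter level is merely conservative.* This largely stands. In the table of RR 0.62 against 1.0, moving from 0.025 to 0.05 adds about 8 to 10 points, and with 400 evaluable per arm about 10 to 11. Correcting the level alone would still leave the condition unmet in most of those trials. The divisor is a real mismatch but the smaller of the two problems. It is also tempting to read it as left over from a dropped second factor, but nothing in the Protocol shows that.

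**Conclusion.** The point holds on the text of sections 5.2, 7.9.5 and 7.9.6. The division by 2 has no second comparison behind it, and the rule for estimating stratum effects is narrower than the objective it serves.

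The size depends on inputs the Protocol does not supply. Under the assumed contrast, with 15% loss and splits from 20:80 to 50:50, the planned stratum estimates would be triggered in roughly a quarter of trials or fewer at the written level. That full loss is the planning maximum, since the Protocol expects about half of it, and having no loss raises the figure only to 30% at an even split. Only very strong interactions, such as RR 0.40 against 1.0 with near-even strata, trigger them in most trials, so this is not a statement about every scenario.

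The change should be made, because a named secondary objective is affected and the remedy is nearly free. The primary analysis, the sample size and trial conduct are not touched.

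**What to change.** In section 7.9.6:

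1. Delete the condition on a significant test. State that the 17P hazard ratio with 95% CI will be reported in both ART-timing strata from the Cox interaction model already planned, whatever the interaction result.
2. Report the single interaction p-value beside the two estimates, judged at 0.05. If 0.05/2 is intended, name the second comparison that justifies it.
3. If Kaplan-Meier risk ratios by stratum are also wanted, to match the primary analysis, label them as a different scale from the Cox interaction test.

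The cost is an edit of about two sentences and two more estimates in a table. The downside is that a reader may over-read one stratum in isolation. The interaction p-value shown alongside limits that.
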